## Abstract

**Background:**

Single-lead, smartphone-based mobile electrocardiograms (ECGs) have the potential to provide a noninvasive, rapid, and cost-effective means of screening for atrial fibrillation (AFib) in outpatient settings. AFib has been associated with various comorbid diseases that prompt further investigation and screening methodologies for at-risk populations. A simple 30-second sinus rhythm strip from the KardiaMobile ECG (AliveCor) can provide an effective screen for cardiac rhythm abnormalities.

**Objective:**

The aim of this study is to demonstrate the feasibility of performing Kardia-enabled ECG recordings routinely in outpatient settings in high-risk populations and its potential use in uncovering previous undiagnosed cases of AFib. Specific aim 1 is to determine the feasibility and accuracy of performing routine cardiac rhythm sampling in patients deemed at high risk for AFib. Specific aim 2 is to determine whether routine rhythm sampling in outpatient clinics with high-risk patients can be used cost-effectively in an outpatient clinic without increasing the time it takes for the patient to be seen by a physician.

**Methods:**

Participants were recruited across 6 clinic sites across the University of Florida Health Network: University of Florida Health Nephrology, Sleep Center, Ophthalmology, Urology, Neurology, and Pre-Surgical. Participants, aged 18-99 years, who agreed to partake in the study were given a consent form and completed a questionnaire regarding their past medical history and risk factors for cardiovascular disease. Single-lead, 30-second ECGs were taken by the KardiaMobile ECG device. If patients are found to have newly diagnosed AFib, the attending physician is notified, and a 12-lead ECG or standard ECG equivalent will be ordered.

**Results:**

As of March 1, 2024, a total of 2339 participants have been enrolled. Of the data collected thus far, the KardiaMobile rhythm strip reported 381 abnormal readings, which are pending analysis from a cardiologist. A total of 78 readings were labeled as possible AFib, 159 readings were labeled unclassified, and 49 were unreadable. Of note, the average age of participants was 61 (SD 10.25) years, and the average self-reported weight was 194 (SD 14.26) pounds. Additionally, 1572 (67.25%) participants report not regularly seeing a cardiologist. Regarding feasibility, the average length of enrolling a patient into the study was 3:30 (SD 0.5) minutes after informed consent was completed, and medical staff across clinic sites (n=25) reported 9 of 10 level of satisfaction with the impact of the screening on clinic flow.

**Conclusions:**

Preliminary data show promise regarding the feasibility of using KardiaMobile ECGs for the screening of AFib and prevention of cardiological disease in vulnerable outpatient populations. The use of a single-lead mobile ECG strip can serve as a low-cost, effective AFib screen for implementation across free clinics attempting to provide increased health care accessibility.

**International Registered Report Identifier (IRRID):**

DERR1-10.2196/52647

## Introduction

### Addressing the Use of Sinus Rhythm Screening

Cardiovascular disease is the leading cause of death in the United States [1]. It is estimated that by 2030, 43.9% of US adults will have at least 1 type of cardiovascular disease [2]. Atrial fibrillation (AFib) is the most common sustained arrhythmia diagnosed in clinical practice [3,4]. It reduces a patient’s quality of life and increases morbidity and mortality rates, which may lead to an increased risk of heart failure [5].

The prevalence of AFib is 2.3% in people older than 40 years and 5.9% in those older than 65 years, and about 70% of individuals with AFib are between 65 and 85 years of age [6]. The prevalence of AFib increases with age, and considering the present aging population, an epidemic is expected to occur within the next 10-20 years [4]. Patients with chronic kidney disease show a higher prevalence of AFib, with ranges estimating from 16% to 21% for patients not on dialysis and 15%-40% for patients on dialysis [4,7]. Currently, about 2.7-6.2 million people in the United States have AFib, but as the population continues to age, an estimated 6-12 million people in the United States will be affected [4,7]. However, since AFib can be asymptomatic, it may remain undiagnosed until or after complications occur. Waiting for these complications to arise may be detrimental, as AFib has a 5-fold increased risk of stroke [8,9]. Developing a low-cost and efficient screening protocol for primary care and outpatient clinics may help to improve the detection of AFib and may help prevent the risk of stroke. In fact, implementing proper treatment, such as the use of oral anticoagulants after a diagnosis of AFib, can decrease the risk of stroke by 60% [5].

To diagnose AFib, an electrocardiogram (ECG) reading must show irregular R-wave intervals without distinct P waves [10,11]. Standard 12-lead ECGs are costly and time-consuming devices that are used to detect AFib [12,13]. The development of new devices like the single-lead portable, phone-based KardiaMobile device (AliveCor) may be an efficient and cost-effective alternative to the standard 12-lead ECGs that can potentially offer feasible mass screenings for AFib [14,15]. The standardization of mass screenings for AFib in primary and outpatient clinics can thus help improve the implementation of prevention strategies for cardiovascular diseases [16]. Costs, availability, and time required to use ECG machines are prohibitive factors for conducting regular ECGs [17,18].

Timely identification of AFib plays a crucial role in reducing mortality rates, allowing for an opportunity to cardiovert the patient, start the patient on anticoagulant therapy, and apply catheter ablation techniques [19,20]. AFib is often asymptomatic; thus, many cases may go undiagnosed without any screening mechanisms in place. A retrospective modeling study published in 2018 discovered that 1.3% of older patients and 0.9% of working-age adults went undiagnosed for AFib [8,21]. To decrease this gap of undiagnosed cases and improve the health care of patients, it is primordial to implement feasible screening and prevention strategies. A 2018 study published in the *Journal of Arrhythmias* reviewed portable out-of-hospital ECG devices [22,23]. Of the devices that they reviewed, AliveCor’s KardiaMobile device was determined to be accurate in measuring QTC wave intervals on ECG and was found to have a sensitivity of 98.5% and a specificity of 91.4% in pharmacy patients older than 65 years [24,25].

### Specific Aims

The aim of this study is to demonstrate the feasibility of performing Kardia-enabled ECG recordings routinely in outpatient settings in high-risk populations and its potential use in uncovering previously undiagnosed cases of AFib. Specific aim 1 is to determine the feasibility and accuracy of performing routine cardiac rhythm sampling in patients deemed at high risk for AFib. Specific aim 2 is to determine whether routine rhythm sampling in outpatient clinics with high-risk patients can be used cost-effectively in an outpatient clinic without increasing the time it takes for the patient to be seen by a physician.

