## Methods

### Participants

For this study, we will recruit approximately 655 participants from each of the selected University of Florida (UF) outpatient specialty clinics. This sample size was specifically chosen as a result of statistical analysis that suggests this study population would indicate a powered study. There is no control group, as this was an observational study. Due to the nature of our enrollment process, which does not require a follow-up visit, we expect a <1% attrition rate, reaching a desired ~655 samples per site based on our power analysis. Study participants will be between the ages of 18 and 99 years.

Eligible participants are any patient visiting the UF Nephrology Clinic, UF Sleep Clinic, UF Neurology Clinic, UF Ophthalmology Clinic, UF Urology Clinic, and UF Pre-Surgical Center. Patients with a history of AFib will not be excluded from the study, as they provide valuable data on potential risk factors and may be prone to AFib recurrence. Participants were only excluded if they were younger than 18 years of age, a leg or hand amputee, a paralyzed person, unable to consent, or unable to read and comprehend English.

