### Procedure

Upon obtaining informed consent, research assistants will use the KardiaMobile single-lead ECG by AliveCor to obtain an ECG reading. Before conducting the examination or filling out a cardiovascular-specific screening survey, participants will have to consent to the study. Any questions regarding the survey will be answered by study personnel present in the room. The Mobile ECG recording by the KardiaMobile device will take place in the patient waiting room for approximately 30 seconds.

The smartphone single-lead attachment is compatible with the KardiaMobile app, a HIPAA (Health Insurance Portability and Accountability Act)-compliant smartphone phone app that can temporarily save these ECGs. Each ECG recorded from a participant will be saved on the UF Dropbox using a randomly generated number that corresponds with the participants’ medical record numbers.

The UF Dropbox cloud-hosting service will only be accessible to study personnel who require viewing the ECGs in order to assess them. Access to the UF Dropbox requires logging into the UF Health VPN and accessing the site via a password combination containing uppercase letters, lowercase letters, numbers, and punctuation. The KardiaMobile smartphone app requires either a 6-digit password login, fingerprint scan, or face ID to access. ECG recordings will not be permanently stored on the device hosting the recording and will be immediately transferred from the smartphone to the UF Dropbox.

Mobile ECGs will not contain any protected health information, and participants who volunteer to be a part of this research will only be identified by a number that corresponds to the number of persons the study is recruiting. For example, the first study volunteer will have their images labeled as “01” as well as “UF Health Clinic” and will have no personal health identifiers attached to their Mobile ECG recording.

The paper files collected will be stored in a secured holding unit after completion by study participants in accordance with the UF’s IRB guidelines. Upon notification of an irregular finding from the KardiaMobile single-lead device, the treating physician for the participant will be informed by research assistants. If the participant does not have a past medical history of arrhythmia, the physician will decide to order a 12-lead ECG to confirm any suspicion of cardiovascular disease.

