#### Primary Measures

##### Detection Accuracy

The researchers will measure the accuracy of the KardiaMobile ECG device by comparing the resulting ECG phenotype (normal, possible AF, unreadable, unclassified, tachycardia, or bradycardia) to the patients’ actual heart health as determined by the standard 12-lead ECG.

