##### Feasibility

Staff members from the different clinic sites will be asked how the incorporation of the mobile ECG device impacted the flow of the clinic. This will provide researchers with information on whether or not this study impacts the length of time it takes for patients to be seen by their physicians, informing us on the feasibility of implementing this device in a clinical setting.

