##### Heart Health

The final section of the questionnaire focuses on the patients’ cardiac health and their experience with a cardiologist. The questions and response choices are as follows:

“Have you personally ever been diagnosed with any of the following cardiac conditions?”Atrial fibrillation, cardiomyopathy, heart stents, congestive heart failure, heart attack, coronary artery disease, hypertension, stroke, and pacemaker or defibrillator“Are you currently being seen by a cardiologist?”Yes: When is your next scheduled appointment? (eg, 03/2030)No: When is your next scheduled appointment with a primary care physician?

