## Results

As of March 1, 2024, a total of 2339 participants have been enrolled. Of the 6 UF Health specialty clinics, 335 were from the UF Health Nephrology Clinic, 466 from the UF Health Sleep Clinic, 597 from the UF Health Ophthalmology Clinic, 526 from the UF Health Urology Clinic, 231 from the UF Health Neurology Clinic, and 184 from the UF Health Pre-Surgical Clinic. The participants’ ages ranged from 18 to 99 years, with an average age of 61 (SD 10.25) years. The average weight of all participants is 194 (SD 14.26) lbs. The race distribution was reported to be 266 (11.42%) African American, 51 (2.18%) Asian, 124 (5.30%) Latino, 1818 (77.73%) White, and 80 (2.61%) others.

The KardiaMobile rhythm strip reported 381 abnormal readings, which are pending analysis from a cardiologist. A total of 78 readings were labeled as possible AFib, 159 readings were labeled unclassified, and 49 were unreadable. Additionally, 1573 (67.25%) of participants report not regularly seeing a cardiologist.

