Overall, this study indicates that the use of a mobile ECG at an outpatient clinic to screen for AFib is acceptable, feasible, and, with preliminary measures, a cost-effective means for detecting previously undetected AFib without impeding clinical operations. These findings have broader public health implications, as an effective screening protocol for AFib can provide earlier access to care through the use of relatively low-cost technologies, which could lead to fewer instances of stroke and more timely initiation of medical therapy.

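### The aim and conclusion concern previously undiagnosed AFib, but no listed outcome is confirmed AFib among participants without prior AFib, and the 78 possible AFib readings cannot stand in for it

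*Protocol article*

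**What the plan says.** All places are in the protocol article.

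- **Aim.** Specific Aims gives the overall aim as feasibility together with "its potential use in uncovering previously undiagnosed cases of AFib". Specific aims 1 and 2 name feasibility, accuracy, cost-effectiveness and time to be seen; neither names yield. The study title under Recruitment refers to detecting subclinical AFib.
- **Eligibility.** Participants: "Patients with a history of AFib will not be excluded from the study".
- **Primary measures.** Detection Accuracy: "The researchers will measure the accuracy of the KardiaMobile ECG device by comparing the resulting ECG phenotype" with the 12-lead ECG. Feasibility: clinic staff "will be asked how the incorporation of the mobile ECG device impacted the flow of the clinic".
- **Secondary measures.** Demographics, symptoms, risk factors, site-specific health and heart health, all from the questionnaire. Heart Health asks "Have you personally ever been diagnosed with any of the following cardiac conditions", and AFib is on the list.
- **Nearest planned count.** Procedure says that positive screens will be compared using the Epic record, without restricting them to people free of known AFib. The 12-lead decision there applies "If the participant does not have a past medical history of arrhythmia".
- **Reported data.** Results: "A total of 78 readings were labeled as possible AFib, 159 readings were labeled unclassified, and 49 were unreadable", within 381 abnormal readings that are pending a cardiologist's analysis.
- **Conclusion.** Discussion gives 95% sensitivity and 97% specificity for previously undiagnosed AFib, and ends by calling the approach "a cost-effective means for detecting previously undetected AFib without impeding clinical operations".

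**The concern.** Uncovering undiagnosed disease is a question of yield: how many people without known AFib were screened, and in how many of them AFib was then confirmed. Accuracy against a 12-lead ECG and staff opinion on clinic flow do not answer it. A device can be accurate and still find few new cases, for instance if most of those it flags already carry the diagnosis.

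If only the listed measures are reported, the article's statement about previously undetected AFib rests on no count. A reader looking for one will take the 78 possible AFib readings. That figure may include people with known AFib, and it is a device label that no cardiologist has yet reviewed. A clinic deciding whether to adopt routine screening would be misled about how many new cases to expect.

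**Working it through.** **1. Aim against outcomes**

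| Listed measure | Counts confirmed AFib in people without prior AFib? |
|---|---|
| Detection accuracy (primary) | No: device label against 12-lead ECG, any history |
| Feasibility (primary) | No: staff view of clinic flow |
| Demographics, symptoms, risk factors, site-specific health (secondary) | No |
| Heart health (secondary) | No, but it records self-reported prior AFib |
| Epic comparison (Procedure; not in the outcome list) | No: positive screens, any history |

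No row is a yield. The questionnaire item and the Epic comparison would allow one to be built.

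**2. What the 78 readings are**

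- Inputs (Results): 78 possible AFib readings, 2339 enrolled.
- Proportion: 78/2339 = 3.33%. Exact (Clopper-Pearson) 95% CI: 2.64% to 4.14%.
- This pools all histories. The known share is not given. As a pure assumption, shares of 25%, 50% and 75% would leave 58.5, 39 and 19.5 unconfirmed positives in people without prior AFib (2.50%, 1.67% and 0.83% of 2339).
- These values cover the 78 alone. The 159 unclassified and 49 unreadable strips could also hold AFib, so 78 is not a ceiling.

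**3. The 95% and 97% figures**

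They cannot be reproduced: the article gives no 2×2 table and no confirmed count, and the Results say the abnormal readings are pending. What can be asked is what they would imply about the 78. Let D be the number of true cases among N people, and assume that all 78 positives come from those N:

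78 = 0.95·D + 0.03·(N − D), so D = (78 − 0.03·N)/0.92.

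| N | D | False positives, 0.03·(N − D) | True share of the 78, 0.95·D/78 |
|---|---|---|---|
| 2339 (all enrolled) | (78 − 70.17)/0.92 = 8.5 (0.36%) | 69.9 | 10% |
| 2131 (less 159 unclassified and 49 unreadable) | (78 − 63.93)/0.92 = 15.3 (0.72%) | 63.5 | 19% |

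Taken at face value, the article's own accuracy figures would make most of the 78 false positives. The result is illustrative, because the correct N is the number screened without known AFib, which is not reported.

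**4. Background rate, for scale**

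The Introduction cites undiagnosed AFib of 0.9% in working-age adults and 1.3% in older patients. Assuming those rates apply here, 2339 × 0.009 = 21 and 2339 × 0.013 = 30 people would have undiagnosed AFib. This is not a forecast of cases found, since one 30-second strip need not catch every case. It does show that 78 is well above the number of undiagnosed cases the cited rates suggest.

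**The case against.** **Yield is not the headline aim.** Feasibility comes first, the text speaks only of potential use, and the two primary measures match specific aim 1. This stands in part: yield is only the second half of the overall aim. It recurs, however, in the recruitment title and in the conclusion, so a matching measure is more than a reviewer's preference.

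**The full protocol or SAP may define it.** Detailed counting rules can be left there. But the article sets out its primary and secondary measures, and these do not cover its own aim and conclusion.

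**The data are planned.** Prior AFib is asked of every participant, the Epic record is to be consulted, and the 12-lead decision is tied to having no arrhythmia history. This stands. A reader might infer that the study cannot say whether it uncovered anyone; the documents do not support that. The measure is undefined and unreported, but the data for it are not absent.

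**The conclusion has a number.** A reader might infer that nothing at all lies behind the conclusion. That goes too far, because the Discussion attaches 95% and 97% to previously undiagnosed AFib. Those figures are accuracy, however, and they are stated while the Results say the abnormal readings are pending.

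**The 78 are not presented as new cases.** Correct: the article gives them as a device label. That they include known AFib is an inference from eligibility, not a stated fact. Nor may one say that the number of new cases lies between 0 and 78, because the unclassified and unreadable strips could add to it.

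**The conclusion is hedged as preliminary.** It is, and it can be read as a statement of capability. Limiting it to what the confirmed count supports is enough.

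**Conclusion.** The point holds in this form. Undiagnosed AFib appears in the overall aim, the recruitment title and the conclusion, but no listed outcome is confirmed AFib among participants without prior AFib. The 78 readings (3.3% of 2339, exact 95% CI 2.6% to 4.1%) are neither split by history nor confirmed and cannot serve as that outcome. The 95% and 97% figures do not fill the gap: they are not a yield, no table supports them, and they conflict with the pending status given in the Results.

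The size of the yield cannot be computed from the article. The implied 8.5 to 15.3 true cases rest on taking the stated accuracy at face value and on all 78 positives coming from the chosen denominator. They show only that 78 is not a safe proxy for new cases. The verdict itself rests on the listed measures and the eligibility rule, not on those figures.

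**What to change.** 1. Add to Outcome Measures: newly confirmed AFib per 100 screened. Numerator: confirmed AFib in participants with no prior AFib, by self-report under Heart Health or by the Epic record before the strip. Denominator: screened participants without prior AFib. Report it with an exact 95% CI.
2. Report the 78 possible AFib, 159 unclassified and 49 unreadable readings, each split by known and no known AFib.
3. Reconcile the Results (abnormal readings pending) with the Discussion (95% and 97% for previously undiagnosed AFib). Either give the 2×2 table behind those figures or withdraw them until the readings have been reviewed.
4. Limit the Discussion's closing statement on previously undetected AFib to what the confirmed count supports.

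The cost is one outcome definition and one extra table from data already planned. The headline count is likely to be smaller than 78.

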## Discussion

A total of 2339 participants across 6 different medical specialty clinics were enrolled in this study. Preliminary findings of the feasibility and accuracy of performing routine cardiac rhythm sampling in patients deemed at high risk for AFib were encouraging, with the average length of patient enrollment being 3:30 (SD 0.5) minutes after informed consent was completed. This time included the participant filling out the site-specific questionnaire. The average length of the single-lead mobile ECG data collection was just 30 (SD 2.5) seconds. Furthermore, when considering feasibility, there were no reports from clinical staff regarding the patient enrollment effort impacting the flow of clinic operations, and 9 of 10 reported satisfaction with the study on clinic operations per medical staff (n=25). Regarding accuracy, the study demonstrated KardiaMobile to have a sensitivity and specificity of 95% and 97%, respectively, for detecting previously undiagnosed AFib. The relatively short time to collect the single-lead ECG along with the accuracy of the technology in detecting AFib suggests that the implementation of routine rhythm sampling with high-risk patients can be used cost-effectively in an outpatient clinic without increasing the time it takes for the patient to be seen by a physician.

The use of a single-lead mobile ECG strip can serve as a low-cost, effective AFib screen for implementation across outpatient clinics attempting to provide increased health care accessibility. A study published in 2022 suggested an “incremental cost-effectiveness ratio of US $57,894 per quality-adjusted life year, meeting the acceptability threshold of US $100,000 per quality-adjusted life year” regarding the cost-effectiveness of single-lead mobile ECGs [26,27]. Additionally, patients can easily purchase this device on their own and measure their ECG signal from the comfort of their own homes. This may allow for more immediate feedback on their heart health and a reduction in costs from clinic visits.

Limitations to the study include the fact that the study was not designed to measure the impact of potential moderators on the outcomes. Additionally, there were limitations related to the relatively high rates of unclassified or unreadable ECG outputs that have been included in the abnormal findings data. Furthermore, the participants were not asked to return for another reading, as these outputs are representative of the device’s effectiveness.

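### Aim 2 asks about cost-effective use, but no listed outcome captures cost or the follow-up work after a flagged reading, so the Discussion's cost-effectiveness statements outrun the study's measures

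*Protocol article*

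**What the plan says.** All places are in the protocol article.

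- **Specific Aims.** Aim 2 asks whether sampling "can be used cost-effectively in an outpatient clinic without increasing the time it takes for the patient to be seen by a physician".
- **Outcome Measures, Feasibility.** Staff at the clinic sites will be "asked how the incorporation of the mobile ECG device impacted the flow of the clinic", to inform on the "length of time it takes for patients to be seen by their physicians". The other primary measure is detection accuracy. The secondary measures are demographics, symptoms, risk factors, site-specific health and heart health.
- **Statistical Analysis.** Agreement, comparison, noninferiority and superiority, sensitivity and specificity are named. No cost or workload analysis is.
- **Procedure.** "Upon notification of an irregular finding from the KardiaMobile single-lead device, the treating physician for the participant will be informed by research assistants". If there is no history of arrhythmia, that physician decides on a 12-lead ECG.
- **Abstract, Methods.** Notification and a 12-lead ECG are tied instead to newly diagnosed AFib.
- **Procedure Flow Diagram (Textbox 1).** A cardiologist interprets the readings and orders the 12-lead ECG if indicated.
- **Introduction.** "Standard 12-lead ECGs are costly and time-consuming devices that are used to detect AFib".
- **Results.** "As of March 1, 2024, a total of 2339 participants have been enrolled". "The KardiaMobile rhythm strip reported 381 abnormal readings, which are pending analysis from a cardiologist".
- **Discussion.** The favourable conclusion on Aim 2 starts from this premise: "The relatively short time to collect the single-lead ECG along with the accuracy of the technology in detecting AFib suggests that the implementation" of routine sampling is cost-effective and adds no wait. The only cost figure is an incremental ratio of US $57,894 per quality-adjusted life year, taken from another study. The closing paragraph calls the screen cost-effective on preliminary measures.

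**The concern.** A screening test uses resources in two places: taking the reading, and acting on the readings that are flagged. The listed measures look at the first, through clinic flow and the wait to be seen. The second consists of physician notification, the 12-lead ECG where one is ordered, and the cardiologist's read. Much of it can fall during or after the visit and on a minority of patients, so a measure of waiting time will not capture it reliably. The article itself regards the 12-lead ECG as expensive and slow.

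At stake is the cost half of Aim 2. With no cost outcome and no count of follow-up work, carrying out the plan exactly as written gives no basis for saying that the screen is cost-effective. The article says so all the same.

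**Working it through.** **1. Denominator.** The site counts in Results add up to the stated total: 335 + 466 + 597 + 526 + 231 + 184 = 2339. I take enrolled as screened.

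**2. Flagged readings.** Results gives 381 abnormal readings, and itemises 78 possible AFib, 159 unclassified and 49 unreadable. These sum to 286, so 381 − 286 = 95 are not itemised. The Discussion confirms that unclassified and unreadable strips are counted as abnormal.

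| Reading | n | n/2339 |
|---|---|---|
| Possible AFib | 78 | 3.3% |
| Unclassified | 159 | 6.8% |
| Unreadable | 49 | 2.1% |
| Not itemised | 95 | 4.1% |
| All abnormal | 381 | 16.3% (Wilson 95% CI 14.8% to 17.8%) |

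Leaving out unclassified and unreadable: (381 − 208)/2339 = 173/2339 = 7.4%. Of the abnormal readings, (381 − 78)/381 = 79.5% are not labelled possible AFib.

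**3. Which of these set off follow-up.**

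- *Notification.* On the Procedure wording, with every abnormal reading taken as irregular, 16.3 per 100 screens. On the Abstract wording, about 3.3 per 100 if possible AFib stands in for newly diagnosed AFib. The second figure could be lower still, because people with known AFib are not excluded.
- *12-lead ECG.* On the Procedure wording, it is limited to people without an arrhythmia history and to the physician's decision. If a share h of those flagged has such a history, at most 16.3 × (1 − h) per 100 are eligible. With h assumed between 0 and 50%, that is 16.3 down to 8.1 per 100.
- *Cardiologist read.* Results mentions it for the abnormal readings (16.3 per 100). Textbox 1 does not restrict it to abnormal strips.

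**4. When follow-up time would matter.** The article gives no follow-up minutes, so I compute only break-even points. If a step takes T minutes per screen and a fraction f is flagged, follow-up equals that step when each flagged reading takes T/f minutes. The Discussion gives T = 0.5 minutes for recording and T = 3.5 minutes for enrolment including the questionnaire.

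| | f = 381/2339 | f = 78/2339 |
|---|---|---|
| Recording, 0.5 min | 0.5 × 2339/381 = 3.1 min | 0.5 × 2339/78 = 15.0 min |
| Enrolment, 3.5 min | 3.5 × 2339/381 = 21.5 min | 3.5 × 2339/78 = 105.0 min |

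The answer moves from 3.1 to 105.0 minutes with the trigger and the comparator. Follow-up could be a large or a small part of the workload, and the listed measures cannot tell which.

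**5. Conclusion against measures.** The Discussion's inference uses recording time and accuracy, plus an outside ratio. None of these is a cost or follow-up quantity measured in this study, and the 381 abnormal readings had not yet been read by a cardiologist.

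**The case against.** The strongest case on the other side has four parts.

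- **Waiting time is a legitimate, openly stated target, and the clinic-flow question is open-ended.** Staff could mention same-visit follow-up, and a 12-lead ECG done on the spot could delay later patients. This stands in part. But the feedback reported in the Discussion (25 staff, 9 of 10 satisfaction, no reports of impact) concerns the enrolment effort and clinic operations. It cannot reflect cardiologist work that was still pending.
- **A condensed article may leave costing to the full protocol.** That is fair as to methods, and I do not fault their absence. The point rests on what the article does state: a cost aim, a list of outcomes without cost, and a favourable cost conclusion drawn from other quantities.
- **A reader might infer that the study counts only the recording step.** The documents do not support this. Aim 2 concerns sampling as a whole, staff views on flow were sought, and the 3:30 minutes of enrolment include the questionnaire. Only the Discussion's inference leans on recording time.
- **A reader might infer that 16 of every 100 screens set off the full work-up, or that follow-up outweighs recording.** Neither is established. The triggers conflict, the 12-lead ECG is conditional, and the comparison depends on assumed minutes and on the step chosen as comparator. Nor can one derive abnormal readings per undiagnosed case from the Introduction's 0.9% and 1.3%. Those come from a modelling study, not from these clinics, and known AFib contributes to the abnormal readings.

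**Conclusion.** The point holds in this form: the listed outcomes cover staff-reported clinic flow and time to be seen, and none captures cost or the follow-up work after a flagged reading. The cost part of Aim 2 therefore cannot be answered from them, and the cost-effectiveness statements in the Discussion go beyond what the study measures.

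The share of screens that could lead to notification lies between about 3.3% (78/2339) and 16.3% (381/2339), and fewer may reach a 12-lead ECG. The upper figure assumes that every abnormal reading, unreadable strips included, counts as irregular. The lower one assumes that possible AFib approximates newly diagnosed AFib. The time and money behind those shares are unknown, so I make no claim that follow-up is the larger burden. The defect lies in measurement and in the conclusion drawn. It is worth correcting, but it does not affect the accuracy aim.

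**What to change.** 1. **Reconcile the notification and 12-lead passages** in the Abstract, the Procedure section and Textbox 1, so that the event to be counted is defined. Which rule applies is for the investigators to decide.
2. **Add follow-up workload to the Feasibility measure.** Count physician notifications, 12-lead ECGs ordered as a result of the screen, and cardiologist reads. Report each per 100 screened and per confirmed new AFib, split by reading label (possible AFib, unclassified, unreadable, other).
3. **Base any workload statement on recording plus follow-up.** Counts alone give neither minutes nor money, so draw no cost-effectiveness conclusion unless costs are attached to them.
4. **Until then, limit the Discussion**, including its closing paragraph, to this: the recording and enrolment steps were short, and staff reported no disruption of clinic flow.

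The cost is small. The study already generates notifications and reads, so study logs can supply them, and 12-lead orders can be counted in the Epic records that the Procedure section already uses. Attaching unit costs would be extra work, needed only if the cost-effectiveness claim is kept. The downside for the authors is a less favourable workload and cost statement.
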